### Data analysis

As in Objective 1, the association between child pedestrian-MVCs and bicycle-MVCs and potential built environment predictors will be assessed using multivariable Poisson regression analysis. Alternative modelling (e.g. negative binomial, zero inflated Poisson) will be applied if over-dispersion of the response variable exists. The proportion of children using active transportation to school will be included as a predictor variable to account for exposure. Municipality will be included in the model as a covariate and confounding and effect modification of the other predictors, by municipality, will be evaluated using standard techniques.

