### Data collection

Direct observations of active transportation to school will be conducted, as per published methods [28, 29, 34–36]. Two trained observers will count children’s travel mode (e.g., walking, bicycle, scooter, vehicle) to school, complete a site survey, and detail built environment features on road segments near the school. Vehicle speed and volume will be measured using municipal speed tubes. The site survey will include presence of designated drop-off areas and presence of dangerous driving and pedestrian/bicyclist behaviours using a checklist we have used previously [37]. We found high test-retest reliability of these count observations in Toronto (Pearson’s r = .96) [29]. Some covariates will come from the site survey whereas others will be extracted from a spatial database compiling built environment metrics at the school-level using different network distance buffers (e.g., between 500 m and 1.6 km, the most frequent distances in the literature and representing a credible range of child walking distances). Using different buffer distances addresses the modifiable areal unit problem [38–40]. The problem reflects how scale and zoning affects the measurement of the built environment. For example, using a smaller distance buffer may produce unstable results, whereas a larger distance buffer may increase the correlation of different built environment variables (scale effect). A zoning effect exists when different buffer sizes produces dissimilar results [38]. Conducting a sensitivity analysis using different buffer sizes will help inform the accuracy and stability of our results. Metrics to populate objectively measured built environment predictors (3D’s- density, diversity, design) will be calculated from the spatial databases. Each predictor will be assessed within street network based distance buffers around schools:

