### Data analysis

The primary outcome variable is the observed proportion of students arriving at school via active transportation. Direct observations of active transportation to school will be used to generate a numerator (students observed walking, bicycling, and other active transportation). The denominator is total observed non-school bus student arrivals (walking, bicycling, arriving by vehicle, and other). Children arriving by school bus will be excluded as they typically live further than walking distance. With the school as the unit of analysis, active transportation proportions will be modeled with built environment predictors using multivariable regression [41]. Sensitivity analysis will use different street network buffer distances. Categorical variables will be included in the model representing each of the sites (municipalities) to enable inter-jurisdictional comparisons. Separate models will also be estimated for each municipality.

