### Study design/location/participants/recruitment

This project has the same study design, locations, and participating schools as Objective 1, with the outcome variables being injury-related. Regression models will use the same predictors, with the addition of a variable for observed active transportation to school, estimated from Objective 1.

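### Project 2A controls exposure for pedestrian and bicyclist collisions with one pooled, walking-dominated proportion, so cycling exposure is likely poorly controlled in the bicyclist model

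*Protocol article*

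**What the plan says.** Project 2A, Data analysis, names two outcomes: "the association between child pedestrian-MVCs and bicycle-MVCs and potential built environment predictors will be assessed using multivariable Poisson regression analysis". I read this as one model per outcome, although the article does not spell that out. The same section gives a single exposure term: "The proportion of children using active transportation to school will be included as a predictor variable to account for exposure". Under Study design/location/participants/recruitment, Project 2A takes that term from the school observations: "Regression models will use the same predictors, with the addition of a variable for observed active transportation to school, estimated from Objective 1".

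Objective 1, Data analysis, defines the quantity. The observations are used to "generate a numerator (students observed walking, bicycling, and other active transportation"). For the denominator: "The denominator is total observed non-school bus student arrivals (walking, bicycling, arriving by vehicle, and other"). On bused pupils: "Children arriving by school bus will be excluded as they typically live further than walking distance".

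The raw material is finer than the variable built from it. Under Objective 1, Data collection, two observers record "travel mode (e.g., walking, bicycle, scooter, vehicle) to school". The school-context items listed under Design in Objective 1 include school enrolment and how many pupils are bused. Project 2A carries these over with the other predictors.

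**The concern.** Children at risk of a bicyclist collision are those cycling, and children at risk of a pedestrian collision are those on foot. A single pooled proportion cannot represent both groups unless walking and cycling rise and fall together across schools. Where walking makes up most of active travel, the pooled figure stands in well for walking and poorly for cycling.

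The stake is how cycling infrastructure is read. Separated paths are among the Objective 1 road-infrastructure predictors that enter Project 2A. The Spatial analysis section of Project 2C itself recognises that a bicycle lane can pull riders in from adjacent streets. If a facility attracts cyclists and cycling volume is not captured, bicyclist collisions can rise simply because more children ride there. A facility that lowers the risk per rider could then look neutral or harmful. The Background faults earlier bicycling research for measuring exposure inadequately. Results from Objectives 1 and 2 also feed the municipal reports and the toolkit in Project 3B.

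**Working it through.** **No figure to reproduce.** The article gives no number for this point. The one computed figure in Project 2A, 120 to 140 schools, does not depend on how exposure is defined.

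**Inputs from the article.** Walking rates by school ran from 28% to 98% with a mean of 67% (Objective 1, Sample size). If those rates carry over, all other modes together make up at most 100 − 67 = 33% at the average school and 100 − 98 = 2% at the highest.

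**Inputs assumed, because the article does not give them.**
- Between-school SD of walking share, s_W: 12 to 17.5 percentage points. The upper value is the stated range divided by four: (98 − 28)/4 = 17.5.
- Between-school SD of bicycling share, s_B: 1 to 4 points.
- Correlation r between walking and bicycling share: −0.3 to +0.6.
- Other active modes are left out for simplicity, so pooled share = walking + bicycling.

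**Formula.** Correlation of pooled share with bicycling share = (r·s_W + s_B) / √(s_W² + s_B² + 2·r·s_W·s_B). For the correlation with walking share, the numerator becomes (s_W + r·s_B).

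**Worked cases.**
- s_W = 17.5, s_B = 1, r = 0: 1/√(306.25 + 1) = 0.06, R² = 0.003.
- s_W = 12, s_B = 4, r = 0: 4/√(144 + 16) = 0.32, R² = 0.10. With walking: 12/√160 = 0.95.
- s_W = 12, s_B = 4, r = 0.6: (7.2 + 4)/√(144 + 16 + 57.6) = 11.2/14.75 = 0.76, R² = 0.58.

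**Correlation of pooled share with bicycling share (R² in brackets), and with walking share:**

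| s_W, s_B | r = −0.3 | r = 0 | r = 0.3 | r = 0.6 | with walking |
|---|---|---|---|---|---|
| 12, 1 | −0.22 (0.05) | 0.08 (0.01) | 0.37 (0.14) | 0.65 (0.42) | about 1.00 |
| 12, 4 | 0.03 (0.00) | 0.32 (0.10) | 0.55 (0.31) | 0.76 (0.58) | 0.94 to 0.98 |
| 17.5, 1 | −0.25 (0.06) | 0.06 (0.00) | 0.35 (0.12) | 0.63 (0.40) | about 1.00 |
| 17.5, 4 | −0.07 (0.01) | 0.22 (0.05) | 0.48 (0.24) | 0.72 (0.52) | 0.97 to 0.99 |

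Over this range the pooled proportion is always close to the walking share. For bicycling it runs from no information, or a slightly inverse relation, to a moderate proxy.

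**Illustration (assumed shares).** Two schools each have 70% active arrivals, one with 1% cycling and the other with 10%. Both get an exposure value of 0.70, while the cycling share differs tenfold.

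**Busing check.** With bus shares assumed uniform up to 40%, a simulated regression of the log active share of all pupils on the pooled proportion alone gives R² = 0.75. Adding bus share raises it to 0.98. For bus shares up to 20% the values are 0.92 and 0.97. Bus share can be formed from the two school-context predictors already listed.

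**The case against.** **The article is condensed.** Exact covariate coding could sit in a fuller plan, and Project 2C already stratifies by travel mode. That has some weight, but the point does not rest on silence: the Objective 1 and Project 2A sections define one pooled variable and assign it the exposure role.

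**Not shown to be uncontrolled.** A reader might infer that bicyclist exposure is effectively uncontrolled. The article does not support that. It gives no cycling share and no walking–cycling correlation, and if the two move together the pooled term does moderate work. Only poor control is likely.

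**Busing and the pedestrian model.** A reader might also infer that pedestrian exposure is misstated, because bused pupils are left out of the proportion while collision rates use the census population of the buffer. This does not stand either. The pooled share follows walking closely. Busing and enrolment are listed predictors that carry into Project 2A. The exclusion is reasoned: bused children are said to live beyond walking distance, so many may lie outside the buffer and its census count. Rescaling the proportion to all pupils could therefore worsen the match.

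**Limits of a cycling term.** Two reservations stand in full. Project 2A uses ten years of collisions in the buffer with no stated restriction to school travel, so arrivals by bicycle are themselves only a proxy. And if infrastructure attracts cyclists, cycling volume may lie on the pathway to collisions, so adjusting for it changes the question from total effect to risk per rider.

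**Conclusion.** The point holds for the bicyclist model. As written, its exposure term is a pooled proportion that mainly measures walking, although mode-specific counts are collected. Under the assumed spreads it captures 0.3% to 10% of the between-school variance in cycling share with no walking–cycling correlation, and from about 0% to 58% over the full assumed range. The conclusion that it is a weak proxy rests on two assumptions: the earlier walking rates carry over to these schools, and walking and cycling are not strongly positively correlated across them. It does not extend to the pedestrian model, provided the busing and enrolment predictors are kept. This is an inexpensive improvement that serves the plan's own aim of accounting for exposure. It is not a defect that invalidates Project 2A.

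**What to change.** In Project 2A, Data analysis, replace the single exposure term with mode-specific terms from the existing observations: the observed bicycling share (or count) in the bicyclist-collision model and the observed walking share in the pedestrian-collision model. Keep the pooled proportion as a sensitivity analysis in both. Report the bicyclist model with and without the cycling term, and state that the first addresses risk given cycling volume and the second the total association. State that the number of bused pupils and school population stay in the 2A models, and leave the proportion on its present denominator.

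No extra data collection is needed; the cost is a changed covariate definition and some additional reporting. The drawbacks are that cyclist counts will be small and noisy at some schools, and that school-arrival counts remain a proxy for all cycling in the buffer. Showing the pooled version alongside lets readers judge both.

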Active transportation by children and youth increases their physical activity, which improves physical and mental health, maintenance of a healthy body weight, academic performance, motor skill development & physical literacy [3] [4]. Furthermore, physical activity habits and attitudes formed in childhood and adolescence are usually carried into adulthood [3–6]. However, only a third of Canadian children walk or bike to school, and longitudinal analyses indicate that the likelihood of using active transportation to school increases until age 10 and then decreases [7]. While it may not be possible for all children to walk to school, many Canadian parents who drive their children would allow them to use active transportation if traffic danger were reduced [8]. In particular, high perceived traffic danger on the school route lowers the odds of frequent walking by 47% [9]. As parents control the choices of school travel mode for children, it is essential to consider both actual and perceived collision risk in relation to the built environment. The analysis of these perceptions, both in children and their parents, leads to a better understanding of school travel choices. Active transportation rates are unlikely to improve without action to reduce traffic related injury risk.

Pedestrian and bicycling injuries are among the leading causes of death and hospitalization for Canadian children and youth [10]. Every year in Canada, 30 child pedestrians and 20 child bicyclists are killed and an additional 2400 child pedestrians and 1800 child bicyclists are injured [11, 12]. Based on 2010 data, child and youth pedestrian and bicycling injuries cost Canadians an estimated $266 million annually ([name]. Parachute, email communication, Dec. 22nd, 2015). Disability related to pedestrian and bicyclist-MVC is higher than that of other injury mechanisms (e.g., sports related injuries) six months post injury [13]. Research has shown a 4-fold increase in severe bicycling injury risk in children and youth with MV involvement [14]. Child specific studies are needed, as previous work shows that the location of child pedestrian injuries differs from other ages [15].

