### Study design

A cross-sectional design will be used that will include primary data collection of active transportation around schools and data from secondary sources related to the built environment, social and individual factors.

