### Data collection

Collisions involving child pedestrians and bicyclists, ages 4–12, will be extracted from the most recent ten years available of police reported child pedestrian-motorvehicle collisions (MVCs) and bicyclist-MVCs in each municipality. Our partners in each municipality will facilitate the access to these datasets. The file will include the geographical coordinates of the collision, which will be mapped onto school buffers. Collision rates will be estimated using census populations within school buffers. Using 10 years of collision data together generates stable, interpretable child pedestrian collision rates as demonstrated in our published work from Toronto [28].

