### Anticipated concerns

It is possible that policies used by police attending incidents vary between cities. To address this concern, we will do a sub-analysis of collisions classified as serious or fatal. Research suggests more accurate reporting of serious and fatal injury by police [44–46]. It is also possible that we will not have the collision data from the same time period for each municipality. We will deal with this by basing models on the most recent years when data are available from all municipalities.

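### Project 2A names only collision models that condition on active travel to school, so its coefficients are not the overall association with collisions per resident child; the same models without that term should be reported alongside

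*Protocol article*

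**What the plan says.** Under Objective 2, Project 2A aims to estimate associations between the objectively measured built environment and child pedestrian and bicyclist collisions with motor vehicles near schools. It takes its schools, design and covariates from Objective 1 (Project 2A, Study design/location/participants/recruitment): "Regression models will use the same predictors, with the addition of a variable for observed active transportation to school, estimated from Objective 1". The Project 2A Data analysis section gives the reason: "The proportion of children using active transportation to school will be included as a predictor variable to account for exposure". The rate denominator is resident children (Project 2A, Data collection): "Collision rates will be estimated using census populations within school buffers".

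In the Objective 1 Data analysis section, the observed proportion arriving by active transportation is the primary outcome and is regressed on the built environment predictors.

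On timing, Objective 1 states: "A cross-sectional design will be used that will include primary data collection of active transportation around schools". The 2A collisions "will be extracted from the most recent ten years available of police reported" collisions. If the cities' records cover different periods, the plan is to respond by "basing models on the most recent years when data are available from all municipalities" (Project 2A, Anticipated concerns).

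**The concern.** One variable has two roles. In Objective 1 the active transportation proportion is a consequence of the built environment. In Project 2A it is an adjustment variable in a model of the same predictors. On the programme's own reasoning it is a likely intermediate: a feature may alter how many children walk or cycle, and more walking or cycling means more exposure to traffic. Holding the proportion fixed removes whatever part of a feature's association with collisions runs through the amount of active travel.

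What remains answers a sensible question: do schools with the feature have fewer collisions than schools without it at the same level of active travel? The question suggested by the stated aim and the census denominator is different: do schools with the feature have fewer collisions per resident child? The article names a model for the first question only and does not say that its coefficients are narrower than the aim.

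The distinction matters for use. Project 3B will turn results from Objectives 1 and 2 into local reports and a toolkit to promote active transportation and/or prevent injuries. A municipality needs to know whether a rate ratio below 1 means fewer collisions among the children living there, lower risk at a given level of walking and cycling, or both.

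**Working it through.** The plan gives no figure for this point. The 2A sample size does not depend on it and is not used here.

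**1. The same proportion in both places**

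| Element | Objective 1 | Project 2A |
|---|---|---|
| Schools | Sampled elementary schools | Same schools |
| Predictors | Density, diversity, design, school context | Same predictors |
| Active transportation proportion | Primary outcome | Added predictor |
| Outcome | That proportion | Collisions, rates on census population |

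The coefficient of a feature in 2A is therefore conditional on the proportion.

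**2. How far the two associations can differ (assumed values)**

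Let D be the rate ratio at fixed active travel, and M the factor by which collisions rise through the extra active travel that goes with the feature. Then overall rate ratio = D x M. The document gives neither D nor M. With D = 0.85:

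- M = 1.00: 0.85 x 1.00 = 0.85, no gap
- M = 1.10: 0.85 x 1.10 = 0.935
- M = 1.20: 0.85 x 1.20 = 1.02

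This assumes that the proportion captures exposure fully. It does not: it counts arrivals at school, excludes school bus arrivals and comes from one survey, whereas the 2A collision extraction is not restricted to school trips. If the proportion accounts for a share f of the pathway on the log scale, the adjusted model estimates D x M^(1-f). With D = 0.85 and M = 1.20:

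- f = 1: 0.85
- f = 0.5: 0.85 x 1.20^0.5 = 0.85 x 1.095 = 0.93
- f = 0: 1.02

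A partial proxy thus gives a smaller gap and an adjusted value between the two targets.

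**3. Simulation check**

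Poisson collisions were simulated at 500 schools, 400 repetitions per setting. From the document: mean active travel 67% (the Objective 1 mean walking rate) and a feature distributed Poisson with mean 0.44 (the traffic calming example in the 2A sample size). Assumed: about 7.4 collisions per school, collisions proportional to active travel, between-school SD 0.6 on the logit scale, and the feature effects below. In the last column the observed proportion carries added error of SD 0.6 on the logit scale.

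| Rate ratio at fixed active travel | Feature effect on logit of active travel | Model without proportion | Model with proportion | With proportion, measured with error |
|---|---|---|---|---|
| 1.000 | 0.4 | 1.12 | 0.99 | 1.05 |
| 0.905 | 0.4 | 1.01 | 0.90 | 0.95 |
| 0.819 | 0.4 | 0.92 | 0.81 | 0.86 |
| 0.819 | 0.8 | 1.01 | 0.80 | 0.90 |
| 0.905 | 0 | 0.90 to 0.91 | 0.90 | 0.91 |

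Where the feature does not affect active travel, the two models agree. Where it does, they separate, and with an imperfect proportion the adjusted estimate lies between the conditional and the overall value. Reporting both is therefore informative in either case.

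**The case against.** The strongest defence is that this is a stated and reasonable target. The Background faults earlier bicycling injury research for not measuring exposure to risk adequately, and 2A adjusts to fill that gap. A condensed article also need not list every model, and nothing in it rules out one without the proportion. All of that stands, and it is why the adjusted model should be kept. What it leaves open is that both places describing the 2A model put the proportion in, while the aim and the denominator point to the overall association and the text does not separate the two.

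It is also fair that the proportion is only a partial proxy, so the 0.85 versus 1.02 contrast is the extreme of the illustration. That stands too, but it means that the adjusted coefficient may match neither target exactly, which is a further reason to show both.

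A reader might infer more than the document supports:

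- *That 2A fails to show whether a feature changes the number of children hit.* 2A is cross-sectional and promises associations, so dropping the proportion would not make it show change. Project 2C addresses collision frequency before and after installation.
- *That active travel is measured at the end of the ten collision years.* This is plausible, but the counts carry no date and the collision window may be cut.
- *That past collisions lower today's proportion.* The Background figure, "high perceived traffic danger on the school route lowers the odds of frequent walking by 47" per cent, concerns perceived danger, not police-reported collisions near a school.
- *That 2A and 2C would contradict each other.* They differ in design, spatial unit and aim, so different results need not conflict.

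**Conclusion.** The point holds as a matter of what is estimated and reported. The only 2A models named give associations at a given level of active travel to school, and these should not be read as the overall association with collisions per resident child. The plan's adjustment is not an error.

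The size cannot be fixed from the document. In the assumed illustration with a conditional rate ratio of 0.85, the overall value is 0.935 or 1.02 for 10% or 20% more collisions through extra active travel. The gap is smaller to the extent that the proportion is a partial proxy, and it vanishes if the feature does not affect active travel. The conclusion rests on two premises: that the built environment influences active travel, which Objective 1 is set up to study, and that more active travel raises collision exposure, which is the plan's reason for adjusting.

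The timing is secondary: a single new survey stands in for exposure over up to ten past years, so the proportion is an imperfect measure for that period.

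**What to change.** Keep the planned model. For each 2A outcome (pedestrian, bicyclist, and the serious or fatal sub-analysis), also fit the same model without the active transportation proportion and report the two side by side. Suggested text for the Project 2A Data analysis section:

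*Each model will be fitted without and with the proportion of children using active transportation. Estimates without it will be labelled as the overall association with collisions per resident child; estimates with it, as the association at a given level of active travel to school.*

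Carry the same labels into the Project 3B reports and toolkit.

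Optionally, repeat the adjusted model on the most recent collision years, closer to the likely time of the survey. This addresses timing only, not the intermediate role of the proportion. It will be less precise, since the plan pools ten years to obtain stable rates.

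No new data are needed. The cost is about twice as many 2A estimates to report, and a short explanation of why the two columns may differ.
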